### Quality control

Quality control visits will be conducted by an independent monitoring team constituted from KSCH using a standardized checklist. Monitoring team will do data quality checks of atleast 10% of enrolled children.

### Data analysis

Final analysis will include all children enrolled in the study. Appropriate quantitative analyses will be used including descriptive statistics (proportion, percentage, mean or median), comparison of difference in proportion for binary outcome using Pearson chi-square and comparison of average change for continuous variable using t-tests. Recovery will be compared for effectiveness of state specific CSAM protocols and locally produced nutrient dense food supplements in four intervention states in comparison to the comparison state. Cox regression method will also be used for this analysis by defining recovery as event, as it can utilize the entire sample size including defaulters or loss to follow up. Other parameters including skinfold, defaulting, death, length of stay, average weekly weight gain and height gain will also be compared between the intervention states and the control state. Subgroup analysis will be done for comparing recovery among children aged 6–23 months and 24–59 months between intervention states and control state. For the sub-sample of body composition, change in fat mass, fat free mass and body water will be compared between the four intervention states and the comparison state. A linear mixed model will be developed for different outcomes (recovery, weight gain, and body composition parameters) adjusting for various random and fixed effects across all sites adjusted for differences at baseline.

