**Methods:**

The longitudinal quasi-experimental study will be undertaken in two purposively selected blocks of one district each in the four intervention states and one comparison state. From each state, 200 SAM children identified using weight-for-length/height z-score (WHZ) < **−** 3 criteria will be enrolled in the study. Their anthropometric data and skinfold thickness will be taken on admission, at sixth week and at discharge by trained field investigators. Other child details, incidence of morbidity and socio-economic details will be collected on admission. To assess food consumption pattern including consumption of locally produced nutrient dense food supplements, dietary assessment, using 24-**h** dietary recall will be conducted on admission, at sixth week and at discharge. In addition, body composition parameters will be assessed for a sub-set of children using bio-electrical impedance analysis on admission and at discharge to analyse changes in total body water, fat-free mass, and fat mass. Post discharge, all study participants will be followed up monthly until 6 months. Atleast 10% of the sample will be checked for quality assessment.

The study’s primary outcome is cure rate defined as children attaining WHZ **≥** -2. Secondary outcomes include mean weight gain, mean length of stay, body composition parameters, relapse and mortality rates. Additionally, process evaluation and cost effectiveness analysis will be conducted.

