#### Secondary research questions

Do state specific CSAM programmes help recovery of a SAM child, as defined by body composition parameters such as fat mass by skinfold thickness and fat free mass, body water by BIA, in each of the four intervention states?What is the relationship between anthropometry and body composition measures in a child suffering from SAM, in each of the five states?Do state specific CSAM programme provide better outcomes in terms of recovery, defaulting, death, length of stay and average weekly weight gain, compared to existing evidence from India?Which of the CSAM programme provides best rate of recovery 6 months after exit from the programme, defined by the relapse and mortality rates?

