### Sample size

The primary outcome of the study is cure rate at 12 weeks (in Chhattisgarh) or 16 weeks (in Telangana, Madhya Pradesh and Odisha) compared to the comparison area. Evidence on CMAM interventions in India testing its efficacy have shown cure rates ranging from 46.7 to 57.4% [19–23]. Another study from India found cure rate among 25–30% children with minimal community based interventions [26]. Hence for the sample size calculation, we therefore chose the expected cure rate with the proposed CSAM interventions of 50% and expected cure rate with existing government nutritional interventions of 25% to estimate the effect size of 25% (50–25%). The sample in each state will comprise of an equal proportion of children from the two age groups (6–23 months and 24–59 months). Using the significance level of 5%, with 80% power to detect the effect size of 25%, a design effect of 1.5 and accounting for 20% attrition due to loss of follow up and mortality, the sample size calculated for each age group of children is 100. Hence, the proposed sample size for the two age-groups of children in each state is 200 children. In total, the study will enroll 1000 children in all the five study states.

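### Mean length of stay partly measures the programme cap and early exits, not only speed of recovery, so it should not be read as showing a better programme

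*Protocol article*

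**What the plan says.** The Abstract (Methods) lists the outcome: "Secondary outcomes include mean weight gain, mean length of stay, body composition parameters, relapse and mortality rates". The third of the Secondary research questions asks whether the state programmes "provide better outcomes in terms of recovery, defaulting, death, length of stay and average weekly weight gain, compared to existing evidence from India", so length of stay stands beside defaulting and death as a sign of a better programme.

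The Data analysis section sets one analysis population, without exception: "Final analysis will include all children enrolled in the study". It then states: "Other parameters including skinfold, defaulting, death, length of stay, average weekly weight gain and height gain will also be compared". The contrast meant there is CSAM states against the control area. The only test it names for continuous data is "comparison of average change for continuous variable using t-tests". The method that can handle children who leave early is tied to recovery: "Cox regression method will also be used for this analysis by defining recovery as event". The linear mixed model is listed for recovery, weight gain and body composition, not for length of stay.

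The maximum treatment duration differs by state. Table 1 gives 12 weeks for Madhya Pradesh and 16 weeks for Telangana, Chhattisgarh and Odisha. The Sample size section instead sets the primary outcome as "cure rate at 12 weeks (in Chhattisgarh) or 16 weeks (in Telangana, Madhya Pradesh and Odisha". Both places have one 12-week state and three 16-week states, but they disagree on which state is which and must be reconciled.

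**The concern.** A stay can end in four ways: cure, default, death, or reaching the cap uncured. Averaged together over all enrolled children, a shorter stay can mean faster cure, more children lost, more deaths or an earlier cap. These carry opposite messages about the programme. Default and death shorten the mean, so a worse result on two items of the third secondary question produces an apparently better result on a third item. A lower cap shortens it for a reason unrelated to how fast children recover.

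At stake is how each state's mean stay is interpreted, both against published Indian figures and when the states' results are set side by side. The primary outcome, cure rate, is not touched by this point.

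**Working it through.** **Plan's own figure.** The article gives no length-of-stay figure. Its sample size supplies the inputs and was checked first. For 50% v 25%, two-sided 5% and 80% power: 7.849 × (0.25 + 0.1875) / 0.0625 = 54.9; × 1.5 design effect = 82.4; × 1.2 for attrition = 98.9. This agrees with the stated 100 per age group, 200 per state.

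**Inputs from the article.** Cure 50% (CSAM) and 25% (existing interventions); cited range 46.7% to 57.4%; caps 12 and 16 weeks; 200 per state; design effect 1.5.

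**Assumptions.** Recovery hazard is constant with 50% cured at week 16; this is varied over 25% to 57.4% cure and Weibull shapes 1 to 2. Default or death runs at a constant rate, 0% to 30% by week 16. Each child's stay runs from admission to first exit of any kind.

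**Formula.** Mean stay = (1 − exp(−k × cap)) / k, where k is the recovery hazard plus the exit hazard.

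**Step 1: cap only.** Recovery hazard = −ln(0.5)/16 = 0.0433 per week, no default.
- Cap 12: (1 − 0.5946) / 0.0433 = 9.36 weeks (SD 3.88)
- Cap 16: (1 − 0.5) / 0.0433 = 11.54 weeks (SD 5.50)
- Gap 2.18 weeks, with identical recovery speed

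At 25% cured, constant hazard: 10.79 v 13.90 weeks. Over the whole grid the gap runs from 1.9 weeks (57.4%, shape 1) to 3.2 weeks (25%, shape 2).

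If a t-test were used with the design effect applied, the effective n is 200/1.5 = 133 per state. The standard error is √((3.88² + 5.50²)/133) = 0.58, the ratio is 2.18/0.58 ≈ 3.7, and rejection is about 96%.

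**Step 2: default only, both caps 16.** Exit hazards are −ln(0.9)/16 = 0.0066 and −ln(0.7)/16 = 0.0223.
- 10% default: 11.02 weeks (SD 5.63)
- 30% default: 9.91 weeks (SD 5.76)
- Shift 1.1 weeks in favour of the programme that loses more children; rejection about 36% after the design effect

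**Step 3: cured children only.** Mean = 1/λ − cap × e^(−λ·cap) / (1 − e^(−λ·cap)), with 1/λ = 23.08.
- Cap 12: 23.08 − 12 × 0.5946/0.4054 = 5.48 weeks
- Cap 16: 23.08 − 16 × 0.5/0.5 = 7.08 weeks

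The cap still moves the mean by 1.6 weeks, so changing the denominator does not solve the problem.

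**Step 4: the proposed measure under the same assumptions.** Proportion cured by week 12 = (λ/k) × (1 − e^(−12k)).
- No default: 1 − 0.5946 = 40.5% whether the cap is 12 or 16, so the cap effect is gone
- 10% default: 0.868 × 0.451 = 39.1%; 30% default: 0.660 × 0.545 = 36.0%. More default now counts against the programme.

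**The case against.** Much of the case on the other side is sound.

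- **The stay of an uncured child is not defined.** A reader might infer that the plan counts a week-2 defaulter as a good two-week stay. The article does not say so. It states a general population and leaves the derivation of this outcome open, which an article may do. The point does not depend on that inference alone: the cured-only alternative also carries the cap effect.
- **No t-test on length of stay is specified.** The t-test sentence concerns average change, and length of stay is not a change score. The rejection rates above therefore describe what would happen if such a test were used.
- **No test of length of stay between CSAM programmes is written down.** The Data analysis section plans intervention states against the control state, and the third secondary question plans comparison with published evidence. The cross-state comparison in the Rationale names cure rate, weight gain, relapse and mortality. A reader might infer that a false between-programme difference is a planned result; the text does not support that. Each state's mean nevertheless carries its own cap and exits into the comparison with published evidence, and into any reading across states. The article gives no published length of stay, so the error in that comparison cannot be sized.
- **Recovery speed is already analysed.** The Cox model uses all children, and defaulting and death are reported in their own right. A reader might infer that the plan has no sound measure of recovery speed, which is wrong. The gap is confined to length of stay itself.
- **Default and death alone are a modest effect.** A reader might infer that they shift the mean by several weeks. At the assumed rates the shift is about 1 week, and most of the gap comes from the cap.
- **That shorter is better is implied, not written.** Listing length of stay among better outcomes needs some direction, and shorter is the only sensible one.

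**Conclusion.** The point holds for how mean length of stay is interpreted. With all enrolled children analysed, caps of 12 and 16 weeks, and no separation of cure from other exits, the mean is partly a measure of the cap and of early loss. The cap alone accounts for about 2.2 weeks at equal recovery speed (1.9 to 3.2 over the range examined). A 20-point difference in default accounts for about 1.1 weeks.

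These sizes rest on assumed recovery curves, on the 50% cure figure placed at week 16, and on default rates that the article does not give. The direction does not depend on them: an earlier cap or earlier exits shorten the mean. Which state has the 12-week cap does not alter the arithmetic, but it decides whose figure is shortened.

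This is one secondary outcome, and the primary cure rate and the planned Cox analysis stand apart from it. The comparison with the control state is not sized here, because the article states no programme cap for an area without CSAM.

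**What to change.** 1. For comparison between programmes or with published results, replace mean length of stay with the cumulative proportion cured by a common 12 weeks among all enrolled children. Count default and death as not cured. Present it beside the Cox recovery analysis already planned.
2. If a length-of-stay figure is wanted, give it only for children cured by week 12 in every state, label it so, and report default and death separately next to it.
3. Do not describe an unrestricted mean stay as evidence of a better programme.
4. Reconcile Table 1 with the Sample size section on which state has the 12-week duration.

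The cost is a change of analysis wording. The measure in item 1 needs the date of discharge as cured, not dates of default, which no section says are recorded. In the 16-week states, cure by week 12 would be read from that discharge date, since Table 2 shows no separate week-12 visit there. The downside is that weeks 13 to 16 are not used in this one comparison; they can be shown separately for the 16-week states.

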### Selection of anganwadi centres

In each participating state, 100 *anganwadi centres* from the two study Blocks will be selected using probability proportion to size (PPS) sampling technique.

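### The named chi-square and t-tests treat children as independent although the sample size assumes a design effect of 1.5, and the planned mixed model closes the gap only in part

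*Protocol article*

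**What the plan says.** Four statements in the protocol article bear on this point.

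- **Sample size.** The calculation includes "a design effect of 1.5 and accounting for 20% attrition due to loss of follow up and mortality". The result is that "the sample size calculated for each age group of children is 100", and so "the proposed sample size for the two age-groups of children in each state is 200 children".
- **Selection of anganwadi centres.** In each state 100 centres "from the two study Blocks will be selected using probability proportion to size (PPS) sampling technique".
- **Data analysis, tests.** The methods listed include "comparison of difference in proportion for binary outcome using Pearson chi-square and comparison of average change for continuous variable using t-tests". Recovery is then to be compared between each intervention state and the comparison state, with Cox regression as an additional method for the same comparison.
- **Data analysis, model.** The section ends with a linear mixed model for recovery, weight gain and body composition. It is to contain random and fixed effects over the sites and to adjust for baseline differences. The level of the random effects is not given, and neither this model nor the chi-square test is called primary.

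**The concern.** The sample size allows for 50% more variance than independent children would give. The tests named for comparing groups allow for none. Children from one centre share a frontline worker, a food supply and a village, so some correlation in cure and weight gain is to be expected.

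If the comparisons are run as named, standard errors are too small, intervals too narrow, and a nominal 5% test rejects too often. This touches the primary outcome (cure) in all four contrasts with the comparison state, and the Discussion section ties scale-up to those results. For the outcomes outside the mixed model's list, the unadjusted tests are the only analysis that the article names.

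**Working it through.** **Inputs from the Sample size section.** "Using the significance level of 5%, with 80% power to detect the effect size of 25" percentage points; "expected cure rate with the proposed CSAM interventions of 50"%; "expected cure rate with existing government nutritional interventions of 25"%; design effect 1.5; attrition 20%. Sidedness is not stated; two-sided is assumed.

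**1. Does the stated sample size depend on the design effect?**

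n = [p1(1-p1) + p2(1-p2)] x (1.960 + 0.842)² / (p1-p2)² = 0.4375 x (2.802)² / 0.25² = 54.9, rounded up to 55.

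55 x 1.5 = 82.5, and 82.5 x 1.2 = 99, which agrees with the stated 100. (Dividing by 0.8 instead of multiplying by 1.2 gives 103.1.) Without the factor 1.5, the variants tried (pooled, unpooled, continuity-corrected, one-sided), each divided by 0.8, give 57.5 to 82.5. So the plan does rest on correlated data.

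**2. What does an unadjusted test do at a given design effect (DE)?**

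True two-sided type I error = 2 x [1 - Φ(1.96/√DE)]. Ratio of the unadjusted to the correct standard error = 1/√DE.

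| True DE | Type I error at nominal 5% | SE ratio |
|---|---|---|
| 1.1 | 6.2% | 0.953 |
| 1.2 | 7.4% | 0.913 |
| 1.5 | 11.0% | 0.816 |

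At 1.5 a nominal 95% interval covers 89.0%, and the correct interval is 1/0.816 = 1.22 times as wide. A beta-binomial simulation under the null (25% in both states, 200 children each) gave 11.2% with 100 centres of 2 at ICC 0.5, and 6.0% and 7.2% at centre-level ICC 0.1 and 0.2.

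**3. Which design effect fits the sampling?**

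DE = 1 + (m-1) x ICC, with m children per cluster.

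- Centre: m = 200/100 = 2, so DE = 1 + ICC. A design effect of 1.5 needs ICC = 0.5. Within one age group m averages 100/100 = 1. Uneven numbers per centre would raise the design effect somewhat.
- Block: m = 200/2 = 100, so 1.5 needs ICC = 0.5/99 = 0.005. For assumed block-level ICCs of 0.02 and 0.05 the simulated type I error is 26% and 43%.

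The protocol gives no ICC and does not say which level the 1.5 refers to. All ICC values here are assumptions.

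**4. What does adjustment cost at the planned effect?**

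With 200 x 0.8 = 160 evaluable children per state and cure rates of 50% and 25%, the half-width is 1.96 x √(0.4375/160) = 10.2 points unadjusted, and 10.2 x √1.5, or about 12.6 points, adjusted. Power for the whole-state contrast at DE 1.5 is still about 97%. With 80 evaluable per age group it is 91% unadjusted and 77% adjusted.

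**The case against.** The strongest reply is that random effects are already planned for recovery, the primary outcome, and for weight gain and body composition. A reader might infer from the named tests that the plan pays for clustering in the sample size and then throws it away. The document does not support that: the mixed model is in the same section. What remains is that its cluster level is unnamed, it has no declared priority over the chi-square test, and it does not list skinfold, defaulting, death, length of stay or height gain.

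A reader might also take 11.0% as the actual error rate. The document does not support that either. The 1.5 is a planning allowance, and at about 2 children per centre it would need an implausibly strong correlation between children of the same centre. The effect of centre clustering alone may be small.

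Thirdly, the list of methods is introduced as not exhaustive, and an article condenses. This excuses silence on the variance estimator of the Cox model, which is therefore not counted as an error. It does not excuse the chi-square and t-tests, because these are stated and conflict with a stated design assumption.

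Finally, a centre-level adjustment does not repair block-level correlation. That is true, and it limits the remedy. It is no argument for tests that assume independence.

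**Conclusion.** The point holds in a limited form. The tests named for between-state comparisons do not match the plan's own design assumption, and the mixed model as described does not settle which analysis carries the inference or at what level clustering enters.

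The consequence is a range: a true type I error of about 6-7% for an assumed centre-level design effect of 1.1-1.2, rising to 11.0% with standard errors 18% too small if 1.5 is the true value. These figures rest on a two-sided 5% level, a normal approximation and ICC values that the protocol does not supply. Block-level correlation could make the error larger, and the document gives no basis for estimating it.

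**What to change.** Amend the Data analysis section before any outcome data are analysed:

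- Name one primary analysis of cure, and make a cluster-adjusted analysis with the anganwadi centre as cluster the inferential one for all between-state comparisons.
- For cure and other binary outcomes (defaulting, death), use a logistic mixed model, GEE or a Rao-Scott chi-square test in place of the Pearson chi-square test and the linear model.
- For continuous outcomes, including skinfold, length of stay and height gain, use a mixed model with a random intercept for centre.
- If Cox regression is used, add a robust variance or a frailty term for centre.
- Keep chi-square and t-tests for descriptive tables only, and report the observed ICC.
- State as a limitation that centre-level adjustment does not remove correlation within blocks, with only two per state, and cannot separate the intervention from the state.

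The cost is wording and slightly wider intervals. The centre is known from the sampling, so no new data are needed. If the true design effect were 1.5, the age-group comparisons would lose the most, as the power figures above show.

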## Methods

### Rationale for the study

Currently in India, some of the state governments have decided to conduct the community-based SAM treatment programme, hereinafter called CSAM, using a variety of locally produced nutrient dense food supplements, which has different energy density and nutrient composition. Locally produced nutrient dense food supplements have been chosen by state governments considering factors such as cost, availability and ease of programming. Equally, the CSAM protocol to be used in each state’s CSAM program varies. Little is known about the effectiveness and quality of recovery of children using these locally produced nutrient dense food supplements to be used under these programmes. Therefore, we propose to assess and compare the effectiveness of these programmes at two levels across five states. First, at the programme level through an assessment of programme outcomes in terms of cure rate, weight gain, relapse and mortality, and second, at the level of the individual child by assessing changes in body composition of the child over the course of treatment. This study also meets the recommendations of the WHO expert group meeting, which agreed that the demonstration of the effectiveness of a food for the treatment of acute malnutrition should not be based solely on anthropometric parameters [24].

There is a need to understand the extent to which recovery as per anthropometric and body composition parameters is achieved in each state compared to the state with no CSAM intervention (comparison state). The policy implications of the proposed study are significant in that they will provide evidence on performance of locally produced nutrient dense food supplements and currently implemented CSAM protocols in different states which will aid states in their efforts to strengthen their existing CSAM protocols and alternative food supplements.

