### Intervention strategy

In general, the State Governments of Telangana, Madhya Pradesh, Odisha and Chhattisgarh will implement community-based management of SAM (CSAM) programme adapted from the WHO guidelines, in addition to the existing government nutrition promotion interventions. The approach will incorporate active and/or passive case-finding and screening for severe wasting by government frontline nutrition and health workers. For uniformity, children with WHZ < -3 will be categorized as experiencing SAM. SAM children will further undergo medical examinations and appetite test to identify complicated and uncomplicated cases. All complicated cases will be referred to the nearest nutritional rehabilitation centres (NRCs) for in-patient management. All uncomplicated cases will be enrolled in the CSAM programme for their community-based management in *anganwadi centres*. While the program’s primary focus is on treatment of children who are severely wasted, key activities also include regular follow up of all enrolled children at the *anganwadi centers*, counseling of caregivers on infant and young child feeding (IYCF), safe water, sanitation and hygiene practices, family planning and child care practices, promotion of vaccinations, appropriate referrals of sick children to NRCs or public health facilities and post discharge follow up. SAM children enrolled in the programme will also be given locally produced nutrient dense food supplements, antibiotics, anthelminthic and micronutrient supplements. Key aspects of the state specific CSAM programme are presented in Table 1. Detailed description of the state specific CSAM protocols and nutritional content of each locally produced nutrient dense food supplement is provided in Additional file 1. In the comparison area, where no CSAM intervention is being implemented, SAM children identified and enrolled in the study will receive the existing government nutrition promotion interventions. The existing program includes provision of double quantity of Take Home Ration (THR)^1^ for severely underweight children (which covers most of SAM children) and identification and referral of SAM children to Malnutrition Treatment Centres (MTCs).

**Table 1 Tab1:** Key aspects of the CSAM protocol that vary per state assessed

States	Screening & Identification	Admission criteria	Maximum treatment duration	Discharge criteria	Nutrient dense food	Post-discharge Follow up

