Telangana	Active screening- once in every quarter Passive screening on all MCH contacts	SAM identification by WHZ < -3SD	16 weeks	WHZ ≥ -2SD	Balamrutam+ under ICDS provision (composition- whole wheat, Bengal gram, roasted groundnut, Jaggery, vegetable oil and added vitamin & minerals) *477 Kcal and 11 g protein per 100 g*	Monthly follow up for 6 months
Madhya Pradesh	Active screening- once in every month Passive screening on VHSND/Health Sub-centre& all MCH contacts	SAM identification by WHZ < -3SD	12 weeks	WHZ ≥ −2SD	Take Home Ration (THR) under ICDS provision by MP Agro. State THR is a mix of cereals, pulses, oil, sugar, milk powder and soya bean. *440 Kcal and 17 g protein per 100 g*	Monthly follow up for 3 months
Chhattisgarh	Active screening- once in every quarter Passive screening on VHSND/Health Sub-centre& all MCH contacts	SAM identification by WHZ < -3SD	16 weeks	WHZ ≥ -2SD	ICDS based modified THR (wheat, soybean, chickpea, sugar, vegetable oil, groundnut, finger millet). *410 Kcal and 12.75 g protein per 100 g*	1st, 3^rd^and 6th month
Odisha	Active screening- once in every quarter Passive screening on VHSND/Health Sub-centre& all MCH contacts	SAM identification by WHZ < -3SD	16 weeks	WHZ ≥ -2SD	Augmented ICDS THR (additional oil, groundnut and whole milk powder). *462 Kcal and 16 g protein per 100 g* 1 egg daily in addition to THR	1st, 3rd and 6th month

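### The plan claims to compare the food supplements as well as the protocols, but each food is used in one state only and the planned contrast is whole package versus none, so a food effect cannot be separated

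*Protocol article*

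**What the plan says.** The Data analysis section names two things whose effectiveness is to be judged, the protocol and the food: "Recovery will be compared for effectiveness of state specific CSAM protocols and locally produced nutrient dense food supplements in four intervention states". The sentence goes on to name the comparison state as the reference. Other outcomes "will also be compared between the intervention states and the control state".

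The Rationale makes a similar promise to policy makers: "they will provide evidence on performance of locally produced nutrient dense food supplements and currently implemented CSAM protocols in different states". The same section acknowledges that the food is not the only thing that differs: "Equally, the CSAM protocol to be used in each state’s CSAM program varies".

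Table 1 (Intervention strategy) lists one food per state. Telangana has "Balamrutam+ under ICDS provision", Madhya Pradesh has "Take Home Ration (THR) under ICDS provision by MP Agro", Chhattisgarh has a modified ration, and Odisha has an augmented ration plus "1 egg daily in addition to THR". The text above the table describes what accompanies the food: "SAM children enrolled in the programme will also be given locally produced nutrient dense food supplements, antibiotics, anthelminthic and micronutrient supplements". It adds caregiver counselling, regular follow-up and referral. The comparison area has no CSAM programme. Its routine services include a doubled Take Home Ration for severely underweight children and referral of SAM cases.

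**The concern.** A statement that a food is effective, or that one food does better than another, needs a comparison in which the food varies while the rest of the treatment stays the same. The article describes no such comparison. If a state's cure rate is read as the performance of its product, a state government could choose a food (the four range from 410 to 477 kcal and from 11 to 17 g protein per 100 g) on evidence that concerns a whole programme in one district. The Rationale says the results should help states with alternative food supplements, so this reading is an intended use.

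**Working it through.** **Inputs.**
- Five states with 200 children each (Sample size).
- One district per state and two purposively selected blocks in each (Study design and setting).
- One food per CSAM state, with the egg in Odisha only (Table 1).
- Children are managed under their own state's guidelines and food (Data collection), so the assigned food does not vary within a state.
- Expected cure is 50% with CSAM and 25% without (Sample size).

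**The plan's own figures.** The planned effect is 50 − 25 = 25 percentage points. The 100 children per age group can be reached with the unpooled two-proportion formula at two-sided 5% and 80% power: (1.960 + 0.842)² × (0.25 + 0.1875) / 0.0625 = 54.9, rounded to 55; 55 × 1.5 = 82.5; 82.5 × 1.2 = 99. Sample size is not the problem here.

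**Planned contrast, CSAM state versus comparison state.** For state *s*:

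observed difference = food(*s*) + rest of package(*s*) + state and district difference(*s*)

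One observed difference has to be divided among three terms. With a difference of 25 points:

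| Food effect | Everything else | Observed |
|---|---|---|
| 0 | 25 | 25 |
| 10 | 15 | 25 |
| 25 | 0 | 25 |

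The data cannot tell these rows apart.

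**Rank check on the 1000-row design matrix.**

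| Terms in the model | Columns | Rank |
|---|---|---|
| State indicators | 5 | 5 |
| State + four foods | 9 | 5 |
| Intercept + four foods | 5 | 5 |
| Intercept + four foods + package | 6 | 5 |
| Intercept + package + four foods + egg + duration | 8 | 5 |

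The third row can be fitted, but each of its food coefficients is just that state's whole difference from the comparison state. Adding the package term adds no rank. The planned mixed model cannot help, because baseline adjustment deals with differences between children and the assigned food is constant within a state.

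**The comparison state is not a no-food control.** It supplies Take Home Ration, so even the food part of the contrast is one ration policy against another.

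**Between CSAM states.** The article describes drugs, micronutrients and counselling in common terms for all four CSAM states, so on the text shown they do not distinguish one of these states from another. The main obstacle is state and district difference. In addition, Odisha has the egg, and Table 1 gives Madhya Pradesh a different duration (12 weeks against 16) and screening interval (monthly against quarterly). The Sample size section instead assigns 12 weeks to Chhattisgarh and 16 to Madhya Pradesh. The two places contradict each other and must be reconciled.

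**The nearest thing to a food contrast.** Chhattisgarh and Odisha match in every column of Table 1 except food and egg. Their difference would be (difference in ration) + egg + (difference between districts). The article does not plan this pair as a contrast, the ration cannot be separated from the egg, and wasting in the two districts is 17.2% and 36.0% (Study design and setting). If the Sample size section is followed, duration differs as well.

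**The case against.** The strongest reply is that the study is framed almost throughout at programme level. The aim, the primary question, the data collection text, the costing and the scale-up discussion all speak of programmes, interventions or strategies. The sentence in Data analysis can be read as describing what each state delivers together, and no test of one food against another is specified. This stands, and it means the primary comparison needs no change. It does not remove the two sentences that name the food as an object of evaluation. The Abstract's discussion also presents the evidence gap as one about these foods, although it describes them as part of the CSAM intervention.

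Two stronger readings are tempting, and the documents do not support them.
- A reader might infer that every CSAM state has its own distinct bundle of drugs, counselling, duration and screening, so that no two states are comparable on anything. The article describes drugs and counselling as general to the four states. Telangana, Chhattisgarh and Odisha share 16 weeks and quarterly active screening in Table 1, and Chhattisgarh and Odisha differ there only in food and egg.
- A reader might infer a defect from the fact that Data analysis mentions no use of the supplement intake data. The article gives their purpose as describing consumption and compliance, and a condensed article need not list every tabulation. Nor would an intake-outcome model repair the claim: 24-hour recall is a noisy measure of one child's usual intake, and intake depends on appetite and illness.

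**Conclusion.** The point holds as a mismatch between claim and design. No planned comparison identifies the effect of a food, and all or none of a 25-point difference could be due to it. This is aliasing and not lack of power, so a larger sample would not help. The planned comparison can support only a statement about each state's package as delivered, set against the comparison area.

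This conclusion assumes that the assigned food is constant within each state, as the Data collection section says, and that the comparison area receives none of the CSAM components, as the Intervention strategy section describes. The detailed state protocols are in an additional file that is not shown. They could add differences between states, but they could not make a food vary within a state while children are managed as described. The primary outcome, sample size, tests and data collection are unaffected.

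**What to change.** - In Data analysis, define the comparison as the effectiveness of each state's CSAM package as delivered (food, co-treatments, counselling, duration and follow-up together) versus the comparison area.
- In the Rationale, limit the claim to packages that include these foods, and say that differences will not be attributed to the food alone.
- Reconcile the treatment durations in Table 1 with those in the Sample size section.
- Optionally, report supplement intake descriptively by state, with the Odisha egg counted. No exploratory model of outcome on intake is needed.

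The cost is a few sentences, with no new data or analysis. The downside is a narrower claim about individual foods, which brings the text into line with the stated aim and primary question.
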